### Recruitment methodology and randomization

Initial recruitment of GP practices was with the support of the partner primary health organization. The GPs were identified using primary health organization and practice lists. All of the GP practices contracted under the partner primary health organization were contacted (*N* = 52) and invited to participate in the study, and an effort was made to contact all of the GPs within these practices by email, telephone or in person. A total of 21 practices consented to participate in the study. To safeguard against gross imbalances in number of GPs per study arm, a cluster randomization schedule was created, with randomization restricted by the numbers of GPs in each practice (two medium-size practices were combined in one stratum to balance one very large practice). Of the 63 GPs who originally consented to participate, 59 completed a single two-hour training session (previously described [19]) and returned a signed consent form. Practices agreeing to take part were randomly assigned to provide either the brief intervention or practice as usual to eligible patients attending their surgeries. To ensure approximately equal numbers of GPs per study arm, randomization of practices was conducted within five blocks, according to the number of participating GPs: one, two, three, four, or more than four GPs. An additional two practices dedicated to youth health that are not part of the partner primary health organization were included and randomized into each arm of the study (i.e., these two practices formed their own stratum). Practices assigned to the practice-as-usual study arm will receive training in the intervention at the end of the study.

### Recruitment procedures

During routine clinical practice, GPs identify people with common mental health problems, who might fulfil study criteria. The diagnosis of common mental health problems is made by the GP. These patients are screened for eligibility (using the K10), and referred to the study. A research assistant then recruits participants by conducting the informed consent procedures and collects pre-treatment (baseline) data. Measures are then collected by mail or email after treatment (8, 12, and 26 weeks). Participants receive compensation (NZ $30 US $21 vouchers, a draw for an iPad) following completion of the final questionnaire, to recompense for time and effort in participating in the study.

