## Methods/Design

We are using a pragmatic two-arm single-blinded, cluster randomized controlled trial of the UBI for mild to moderate mental health concerns compared with practice as usual, in a primary care setting. General practitioners have been randomized by practice to exclusively deliver either the UBI or practice as usual to all their recruited participants. The GPs are treated as the clusters in the study design (while there will be clustering by GP practice, the GPs are being treated as the unit of analysis, as practitioner attribute is anticipated to be a higher source of variability in outcomes.)

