### Participants

This is a real-world trial supported in the framework of existing treatment services. Patients aged between 18 and 65 who are identified by their GPs in a routine appointment as experiencing distress and needing a mental health intervention are eligible to participate. All participants must also score 35 or less on the Kessler 10 (K10) assessment scale, which measures global psychological distress, during their initial GP consultation. These scores were selected to indicate mild to moderate levels of psychological distress. There is no lower cut off score, since initial inclusion is based on the GP identifying a clinical problem that would be managed at the GP level. Previous work in New Zealand general practice using the K10 has demonstrated that clinicians do not select patients with very low K10 scores (<20) for clinical intervention [5]. The K10 demonstrated sensitivity and specificity for anxiety and depressive disorders, where scores exceeding 30 indicate a ‘very high’ risk of having a mental disorder [25]. This study follows previous study protocols [19, 23], where scores falling between 30 and 35 on the K10 were indicative of mild to moderate levels of psychological distress rather than a diagnosis of major psychiatric disorder, and were therefore included. Individuals receiving treatment with anti-depressant or other psychiatric medications are eligible to participate in the study.

Exclusion criteria for patients are non-fluency in English (as the intervention is an English-language based ‘talking therapy’), significant levels of cognitive impairment, as determined by the GP, and recent or acute suicidal ideation (i.e., within the previous 2 weeks). Chronic low level suicidality being managed by the GP does not exclude an individual from participating, except for those individuals who have high current levels of distress, indicated by K10 scores exceeding 35 at baseline. General practitioners are informed of patients who have high scores or suicidality at screening, or for whom referral to appropriate secondary mental health services is indicated, and these patients would not be eligible to participate further in the study. Participants are still eligible to participate if their K10 scores increase above 35 during the study, and if, in the active intervention group, they have also completed two out of three sessions of the UBI.

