#### Analysis

The statistician performing data analysis will be blinded to the intervention or control status of participants (both practices and patients). For the primary outcome, K10 scores at 26 weeks will be compared between the intervention and control groups using a mixed linear models application of analysis of covariance (comparing post-intervention scores between groups, adjusting for intake score as a covariate, and treating GP clusters as random effects). Data analysis will be conducted on an intention-to-treat basis. Missing data for the 26-week follow-ups will be handled through the mixed linear models approach to the data, which allows for participants with missing data for the final follow-up to be included in analyses (this in effect estimates a final outcome value conditional on the observed data at other follow-up times.) This missing data method is valid under the assumption that the missing observations are missing at random, conditional on the observed data [32, 33]. The null hypothesis for this test is that the K10 scores at 26 weeks (adjusted for baseline score) are not different in the intervention and control groups.

To account for stratification by type of practice (youth-health focused practices, in contrast to unrestricted GP practices) we will conduct a sensitivity analysis looking at data just from the unrestricted GP practices (i.e. excluding the two practices in the youth-health stratum).

For the secondary analysis, differences in mean scores on the K10 outcome will also be reported at 8 and 12 weeks (using the same methods as before, within the mixed linear models framework). Analysis of the HADS combined score will utilize the same methods as for the K10 outcome.

The findings of this study will be reported in line with the CONSORT statement, as adapted for cluster randomized trials [34].

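### GPs who know their arm identify the patients, and the primary model's only covariate is intake K10, so selection on other prognostic factors is left in the treatment effect

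*Protocol article*

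**What the plan says.** Methods/Design describes the allocation: "General practitioners have been randomized by practice to exclusively deliver either the UBI or practice as usual to all their recruited participants". Recruitment methodology and randomization adds that "Practices assigned to the practice-as-usual study arm will receive training in the intervention at the end of the study".

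Recruitment procedures then sets the order of patient entry. First, "During routine clinical practice, GPs identify people with common mental health problems, who might fulfil study criteria". Next, "The diagnosis of common mental health problems is made by the GP". The patient is screened with the K10 and referred, and only after that does the research team meet the patient: "A research assistant then recruits participants by conducting the informed consent procedures and collects pre-treatment (baseline) data".

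The Participants section limits entry by age (18 to 65), a K10 ceiling of 35, English fluency, cognitive impairment and recent suicidal ideation. It also gives the partner organisation's access criteria (youth, or from age 25 low income or Māori or Pacific heritage). Within those limits, the GP's judgement decides who is put forward.

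Under Analysis, the primary comparison of K10 at 26 weeks is made by "adjusting for intake score as a covariate, and treating GP clusters as random effects". Outcome measures likewise names baseline K10 as the adjustment. The blinding described under Analysis is that of the statistician. The only sensitivity analysis stated there leaves out the two youth practices.

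**The concern.** In a trial that randomises individuals, the patient is enrolled before anyone knows the arm. Here the recruiting clinician knows it. Even if a GP learned the arm only when the first patient was referred, the target is ten patients per GP, so nearly all patients would be chosen with the arm known.

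The arms also give GPs different reasons to choose. A GP in the intervention arm commits to three structured sessions (30 + 15 + 15 minutes) supported by booklets, and may favour patients who are likely to attend and who suit self-help. A GP in the control arm offers usual care, typically a 15-minute consultation, medication or onward referral, and has no such reason. Whether a problem can be managed at GP level may itself depend on what the GP has to offer.

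If the patients put forward differ by arm in ways that predict the 26-week K10 and that intake K10 does not capture, the difference is counted as treatment effect. A blinded statistician, analysis by intention to treat, GP random effects and leaving out the youth practices do not correct for it.

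**Working it through.** **Inputs.** From Sample size and power analysis: SD 7.5, target difference 6 − 2 = 4 points, 15 GPs per arm, 8 completers per GP, intraclass correlation 0.15, power 80%. Assumed: two-sided 5% test.

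**The plan's own figure.**
- Without clustering: 2 × (1.96 + 0.84)² × 7.5² / 4², which rounds up to 56 per arm.
- Design effect: 1 + (8 − 1) × 0.15 = 2.05.
- Per arm: 56 × 2.05 = 114.8, or 114.8 / 8 = 14.35 GPs, rounded up to 15.
- Total: 15 × 8 × 2 = 240, as stated. Power at this size is 82.3% (normal) or 79.5% (t, 28 df).

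This calculation takes patients to be exchangeable between arms apart from treatment.

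**What a residual difference would do.** The planning standard error is 7.5 × √(2 × 2.05 / 120) = 1.386. Suppose there is no treatment effect and a difference b remains after adjustment. The test statistic is then centred at b / 1.386.

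| b (K10 points) | b / SE | False-positive rate, normal | False-positive rate, t 28 df |
|---|---|---|---|
| 0 | 0 | 5.0% | 5.0% |
| 1 | 0.72 | 11.1% | 10.7% |
| 2 | 1.44 | 30.3% | 28.6% |

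With a true effect of 4 points, a 1-point bias moves power from 79.5% to 93.6% if it favours the intervention, or to 55.2% if it goes against it (t, 28 df).

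The values of b are illustrations; the documents give none. This standard error takes no credit for the precision gained by adjusting for intake K10. A smaller one would make the same b more damaging.

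**What intake K10 does and does not absorb.** Assume K10 reliability 0.8, a slope of 0.6 from underlying distress to outcome, and a second prognostic factor, independent of K10, that correlates 0.3 with outcome. None of these comes from the documents.
- *Selection on severity, 4-point arm difference.* Unadjusted bias is 0.6 × 4 = 2.4 points. After adjustment, 2.4 × (1 − 0.8) = 0.48 remains. Simulation at the planned size (3,000 trials) gave 2.3 and 0.4.
- *Selection on the second factor, 0.5 SD arm difference.* Bias is 0.3 × 7.5 × 0.5 = 1.1 points with or without K10 adjustment. Simulated rejection under no effect rose from 3.1% (the simulated test is somewhat conservative) to 10.8%.
- *Selection on the second factor, 1 SD arm difference.* Bias is about 2.2 points and rejection about 35%.

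So intake K10 removes most of the first kind of selection and none of the second.

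**The case against.** The strongest reply has four parts.

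1. *Entry is not open-ended.* A reader might infer that the K10 ceiling is the only limit on GP choice. The documents do not support that: the age range, exclusions and access criteria also bind, and they narrow the room for selection on age, heritage and deprivation. This stands. It does not remove selection within the eligible pool.

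2. *Severity is already handled.* The Participants section states "There is no lower cut off score, since initial inclusion is based on the GP identifying a clinical problem", and a reader might take the absence of a floor as the source of bias. It adds little: intake K10 absorbs most selection on severity, and the article says clinicians do not choose patients scoring below 20. An analysis restricted to scores of 20 or more would therefore drop few patients and answer a question the model already addresses. This part stands in full.

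3. *More covariates do not reach unmeasured factors.* True. The listed variables help only as far as they predict outcome and track what GPs select on. How much bias they would remove has not been shown.

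4. *Extra covariates and flow tables belong in an analysis plan, and the article commits to CONSORT reporting for cluster trials.* This holds for flow tables and supportive analyses. It does not hold for the primary model, which the article states with intake K10 as its named covariate. Nor can a later plan undo identification after allocation.

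The article also does not say whether patients know the arm when they consent. Self-selection by patients is therefore possible but cannot be read from the text.

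**Conclusion.** The concern holds in a limited form. GPs who know their arm identify and refer the patients, and the stated primary model does not protect against selection on prognostic factors other than intake K10. The Discussion's stated limitation concerns restricted eligibility and does not mention this.

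The size and direction are unknown, and nothing in the documents shows that selection will differ by arm. The figures of about 11% and 29–30% are conditional on assumed residual differences of 1 and 2 points and on the planning inputs. A reader might go further and infer that selection could by itself create or hide the 4-point effect sought. The working does not support that: the largest case, a full 1 SD imbalance in a factor unrelated to K10, gives about 2.2 points. The point is a moderate, correctable weakness in the analysis, together with a design limitation that should be stated.

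**What to change.** Before unblinding:
- Pre-specify that the primary mixed model adjusts, besides intake K10, for baseline HADS total, baseline Work and Social Adjustment Scale, age, Māori or Pacific heritage and NZDep2006. The functioning scale is listed at baseline and NZDep2006 among the sociodemographic data. Age and heritage are needed for eligibility. Intake HADS is implied, because HADS is to be analysed like the K10.
- Keep the model with intake K10 alone as a sensitivity analysis, so that the effect of the added covariates can be seen.
- Report baseline characteristics, and the numbers referred, eligible and consented, by arm and practice as far as they were recorded.
- Name identification of patients after allocation as a limitation.

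The cost is a few patient-level degrees of freedom and a rule for missing covariate values; no new data collection is needed. Selection on unmeasured factors such as motivation would remain. The change must be fixed before unblinding, since covariates chosen with the results in view would not be credible.

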### Intervention

The UBI is a structured and guided self-management program, and can be delivered by a GP after a single two-hour training session. Participants who have consented and completed the intake data collection (K10 and baseline measurements) will receive the GP-led intervention in three short, structured face-to-face sessions (one 30 minute and two 15 minute sessions) over a five to six week period. The UBI is a self-help approach based on structured problem solving and cognitive behavior therapy and is supported by self-help booklets on relationships, bodily stress, breaking habits and stress management. Booklets are provided to the patient after the first session, to be used in the following session. The intervention resources have been adapted to better meet the needs of Māori participants, and include Māori imagery, Te Reo (language), wairua (spirituality), whanau (family) and whakatauki (proverbs), the face-to-face sessions can include whakawhanaungatanga (the process of forming connections), and offer karakia (prayer) at the start. Measures will be collected by the research assistant before (baseline) and after treatment (8, 12, and 26 weeks). Participants can revert to practice as usual following the completion of the brief intervention. Participants can commence mental health medications at any time, or withdraw from the study and change to another intervention pathway during UBI, if deemed clinically necessary by their GP or other healthcare providers. Participants are considered to have completed the intervention if they attended at least two out of the three sessions with their GP. Increasing K10 scores during the study are not a reason for withdrawal for either intervention or control group.

### Practice as usual

Participants in the practice-as-usual study arm will receive GP support delivered according to their practice (and available existing services) as usual. Practice as usual typically consists of supportive counselling in a 15 minute face-to-face consultation, the provision of psychotropic medication, referral to psychological or other counselling options, or referral to relevant community services. All measures will be collected according to the same timescale and methodology as the intervention arm. The UBI is excluded as a component of practice-as-usual arm.

### Outcome measures

The primary outcome measure is the Kessler Psychological Distress Scale (K10) [26, 27] score at 26 weeks (adjusted for score at baseline: see analysis). The K10 is widely used as a clinical outcome measure in primary care and general practice [5]. Higher K10 scores indicate a greater likelihood of meeting criteria for a mental disorder diagnosis [27], meaning reductions in K10 scores post-treatment will represent real change in mental health status.

Secondary outcome measures are:Hospital Anxiety and Depression Scale (HADS) [28]. This measures severity of depressive and anxious symptoms in outpatient hospital settings [28]. Reductions in HADS score will indicate reduced anxiety and depression. Given the nature of ‘sub-threshold’ common mental disorder, the HADS score will use the combined anxiety and depression subscales. Patients in the study are likely to have lower scores than those that might be used for categorical case definition; hence, scores have been used as continuous variables.Comparison of K10 scores by treatment group at 8 weeks and 12 weeks, adjusted for baseline scores (to capture short- and medium-term effectiveness).Work and Social Adjustment Scale [29]: a measure of work, social and relationship functioning) at baseline, 8, 12, and 26 weeks.Sociodemographic data will include the NZDep2006 [30], a New Zealand index of individual socioeconomic deprivation.

All clinicians will be asked to complete measures of satisfaction with the intervention at the end of the study, and a randomly selected group of 20 patients will be asked to complete measures of satisfaction with the intervention at 6 weeks post-intervention. These data will be used to inform further operational development of the tool, should the result of the trial affirm its value to clinical practice.

### Statistical methods

#### Sample size and power analysis

Sample size was calculated using a simulation approach, based on standard deviations from a sample of similarly eligible patients from the UBI development study (standard deviation of post-treatment scores = 7.5; unpublished data). For 80 % power to detect a difference in K10 improvement scores of 6 points in the UBI arm, compared with 2 points in the control arm, would require 15 GPs per arm, each recruiting eight completing patients on average (*n* = 240 total with complete data). Adjusting for loss to follow-up of 20 % gives a recruitment target of ten patients per GP. The simulation settings roughly correspond to an intraclass correlation of 0.15 for considering the clustering of patient scores due to GPs: this corresponds to the intraclass correlation from the unpublished data from the development study. A power analysis for the secondary HADS scale outcome indicated that the study would have 80 % power to detect a difference of 3.2 points between groups (based on a standard deviation for the total score of approximately 6 for a general practice sample [31], with the same sampling design, and assuming a similar intraclass correlation for the HADS scale as used for the K10 measure (empirical data not available)).

#### Analysis

The statistician performing data analysis will be blinded to the intervention or control status of participants (both practices and patients). For the primary outcome, K10 scores at 26 weeks will be compared between the intervention and control groups using a mixed linear models application of analysis of covariance (comparing post-intervention scores between groups, adjusting for intake score as a covariate, and treating GP clusters as random effects). Data analysis will be conducted on an intention-to-treat basis. Missing data for the 26-week follow-ups will be handled through the mixed linear models approach to the data, which allows for participants with missing data for the final follow-up to be included in analyses (this in effect estimates a final outcome value conditional on the observed data at other follow-up times.) This missing data method is valid under the assumption that the missing observations are missing at random, conditional on the observed data [32, 33]. The null hypothesis for this test is that the K10 scores at 26 weeks (adjusted for baseline score) are not different in the intervention and control groups.

To account for stratification by type of practice (youth-health focused practices, in contrast to unrestricted GP practices) we will conduct a sensitivity analysis looking at data just from the unrestricted GP practices (i.e. excluding the two practices in the youth-health stratum).

For the secondary analysis, differences in mean scores on the K10 outcome will also be reported at 8 and 12 weeks (using the same methods as before, within the mixed linear models framework). Analysis of the HADS combined score will utilize the same methods as for the K10 outcome.

The findings of this study will be reported in line with the CONSORT statement, as adapted for cluster randomized trials [34].

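### The primary model omits the strata used to randomise practices, and dropping the two youth practices does not adjust for them; the cost is possible loss of precision, not bias

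*Protocol article*

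**What the plan says.** Under Recruitment methodology and randomization, the protocol article makes the practice the randomised unit: "Practices agreeing to take part were randomly assigned to provide either the brief intervention or practice as usual to eligible patients". The allocation was restricted: "randomization of practices was conducted within five blocks, according to the number of participating GPs: one, two, three, four, or more than four GPs". The stated purpose is logistical: "To ensure approximately equal numbers of GPs per study arm". The same section mentions one stratum in which two mid-sized practices were set against a single very large one. Of two youth-health practices from outside the partner organisation, it says that "these two practices formed their own stratum", one going to each arm.

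Under Analysis, the primary comparison of 26-week K10 is a mixed-model analysis of covariance, "comparing post-intervention scores between groups, adjusting for intake score as a covariate, and treating GP clusters as random effects". No stratum term is named. On stratification by practice type, the stated aim is: "To account for stratification by type of practice (youth-health focused practices, in contrast to unrestricted GP practices) we will conduct a sensitivity analysis". The content of that step is: "we will conduct a sensitivity analysis looking at data just from the unrestricted GP practices (i.e. excluding the two practices in the youth-health stratum". The size strata do not appear in the Analysis section. The secondary K10 and HADS analyses use the same methods.

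**The concern.** When allocation is balanced within strata, differences between strata largely cancel out of the treatment contrast. A model without the strata still counts those differences as residual or between-GP variance. If the strata are related to outcome, the reported standard error is then larger than the true one and the interval wider than it need be.

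The step the article offers is a restriction, not an adjustment. It leaves the primary estimate as it was, describes a narrower population, gives up two randomised practices and does nothing about the size strata. At stake is precision in a trial whose planned size only just reaches its power target.

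**Working it through.** **Inputs from the protocol article.** SD "standard deviation of post-treatment scores = 7.5; unpublished data"; GP-level intraclass correlation 0.15; 15 GPs per arm with 8 completers each; improvements of 6 against 2 points; 80% power; 21 + 2 = 23 practices.

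**Assumed, not in the documents.** Two-sided alpha 0.05, the distribution of practice sizes, the stratum effects, any practice-level variance, and the patients per GP used in each simulation.

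**1. The plan's own sample size.** For a difference of 4 and SD 7.5, 56 patients per arm are needed without clustering. The design effect is 1 + 7 × 0.15 = 2.05. Then 56 × 2.05 = 114.8 per arm, and 114.8 / 8 = 14.35, so 15 GPs per arm and 15 × 8 × 2 = 240. This agrees with the article. Power at 15 GPs per arm is 82.3% (normal) or 79.5% (t, 28 df). The present point does not change this figure.

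**2. Direction and approximate size.** With m patients per GP, a GP mean has within-stratum variance 56.25 × (0.15 + 0.85/m). With J GPs in two equal arms, the variance of the contrast is about 4 × that quantity / J. Leaving out strata with variance s² adds up to s² to the GP-mean variance that the model reports.

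- m = 4: 56.25 × 0.3625 = 20.39. With J = 62, the SE is √(4 × 20.39 / 62) = 1.15. The SE is inflated by at most √(21.39/20.39) = 1.02 at s = 1 and √(24.39/20.39) = 1.09 at s = 2.
- m = 8: 56.25 × 0.25625 = 14.41. The inflation is at most √(15.41/14.41) = 1.03 at s = 1 and √(18.41/14.41) = 1.13 at s = 2.

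These are ceilings, because a handful of unequal strata realise less than the full s² among the GPs.

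**3. Simulation of a GP-level analysis with no practice-level variance** (23 practices, 62 GPs, 4 patients per GP, 4,000 null runs per setting).

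| Size-stratum SD | Type I error without / with strata | Mean model SE without / with | Ratio |
|---|---|---|---|
| 0 | 5.1% / 5.2% | 1.140 / 1.140 | 1.00 |
| 1 | 4.4% / 4.7% | 1.163 / 1.141 | 1.02 |
| 2 | 3.8% / 5.0% | 1.219 / 1.142 | 1.07 |
| 3 | 3.0% / 5.4% | 1.310 / 1.142 | 1.15 |

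A second run with 22 practices, 54 GPs and 8 patients each gave 4.5% / 5.2% at SD 1 and 3.0% / 5.0% at SD 2, the same direction.

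**4. Which SDs are credible.** The article's figures imply a total between-GP variance of 0.15 × 56.25 = 8.4. A stratum SD of 1 is 1/8.4 = 12% of that, an SD of 2 is 4/8.4 = 47%, and an SD of 3 (variance 9) exceeds it. SD 1 is the more compatible setting.

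**5. With practice-level variance.** Here a practice share of 0.05 was assumed within the intraclass correlation, again with 22 practices, 54 GPs and 8 patients each, and GP as the only random effect.

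| Stratum SD | Type I error without strata | With strata |
|---|---|---|
| 1 | 10.0% | 11.9% |
| 2 | 7.4% | 11.2% |

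The variance added by leaving out the strata partly masks the practice variance that the GP-only model ignores. Adding the strata alone removes the mask. In the setting of step 3, an added practice SD of 1.5 points gave about 9% with or without stratum terms.

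**6. What the youth exclusion achieves** (setting of step 3).

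- Youth shift of 8 points, no size effect: type I error 3.3% in the primary model and 5.0% after exclusion. It works for practice type alone.
- Youth shift of 4 points, size SD 2: 3.2% in the primary model and still 3.4% after exclusion. Power for an illustrative 2.5-point difference is 51% in the primary model, 50% after exclusion and 58% with stratum terms.

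**7. Cost of the stratum term.** In an analysis of 23 practice means, five extra terms take the degrees of freedom from 21 to 16 and the t quantile from 2.08 to 2.12, a ratio of 1.02. Simulated half-widths with uninformative strata were 2.76 and 2.81 points, also a ratio of 1.02.

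**The case against.** The strongest case against has four parts.

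- **The size strata may not be prognostic.** They were chosen to equalise GP numbers, and nothing in the article links practice size to K10 course. Intake K10 may absorb part of any difference. This stands, and it is why the loss may be near zero.
- **The sentence on stratification claims only practice type.** For that alone, exclusion does remove the youth-versus-other variation (step 6). With one youth practice per arm, showing results without them is sensible. This stands as a reason to keep the analysis. It does not make it an adjustment of the primary estimate, and the size strata stay unaddressed.
- **The detail could sit in an analysis plan not shown.** This does not carry. The article names the model terms and says how stratification by practice type will be handled, and that stated method is the problem.
- **Practice-level clustering matters more.** This stands. Practices were randomised, but only GPs are random effects, so the stratum term cannot be the whole remedy.

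A reader might infer that the planned test is conservative overall, or that one extra term would put it right. Step 5 shows the reverse can hold. A reader might also infer a large loss from an analysis of practice means, where a stratum SD of 2 gives type I error of 2.5% and half-widths of 3.19 against 2.80 points. That is not the planned model, and an SD of 2 is large against the article's between-GP variance. Nothing supports a reading that the omission biases the estimate.

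**Conclusion.** The point holds in a limited form. The randomisation strata are absent from the primary model, and the youth exclusion neither adjusts the primary estimate nor deals with the size strata.

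The treatment estimate is not biased by this. The consequence is a standard error that is too large if the strata are prognostic: about 2 to 3% at a stratum SD of 1 K10 point, 7% in simulation at SD 2 with four patients per GP (ceiling 13% with eight), and none if the strata carry no information. These figures assume no practice-level variance and rest on stratum effects that the documents do not give.

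If practice-level variance exists, whether the test is conservative or anti-conservative depends on both omissions, so they should be corrected together.

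**What to change.** - Add the randomisation strata as fixed effects in the primary K10 model and in the secondary K10 and HADS models. Take them from the schedule as actually used, including the youth stratum and the stratum pairing two mid-sized practices with the very large one. The article does not say how that stratum sits among the five size blocks, so coding by GP count alone could misclassify those practices.
- In the same change, add a practice-level random effect, or use another form of practice-level inference. The stratum term should not go into a GP-only model by itself.
- Keep the analysis without the youth practices, described as a robustness check on population rather than as accounting for stratification.

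The stratum term uses a few practice-level degrees of freedom (five if there are six strata) and widens the interval by about 2% if the strata are uninformative. The practice-level term may widen it further where practice variance exists; that is the price of matching inference to the randomised unit. Recruitment and the stated sample size figure are not touched by the stratum term.
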